## Rationale for the choice of the patient cohort

If the hypothesis is true, the most benefit would be at the time of highest virus replication in the lung cells. Due to the problem of longitudinal and multiple testing from the lower respiratory tract, it is not fully known when this phase occurs. In the phase of intensive care, the virus replication may be less prominent and it may be too late to get an effect from reducing TMPRSS2 by enzalutamide. The inclusion will therefore be for patients with confirmed COVID-19 infection having mild to severe symptoms with no need of mechanical ventilation but that may be in need of extra oxygen.

In Sweden the majority of patients have symptoms upon testing. Most patients will have mild course of the disease and will not be in need of treatment. Risk of having worsening symptoms has been shown to be in association with higher age and/or other risk factors, such as obesity, heart disease, increased number of other diagnoses. We have therefore set an age limit of at least 50 years. In frail patients, any effects on the respiratory function may be fatale but the most benefit of reducing the virus efficacy may be for patients with several other diagnoses. To balance this, we have chosen to include patients with an estimated expected survival prior to COVID-19 infection of 1 year.

Another consideration of the age limit is to exclude patients with low risk of needing intensive care and/or risk of death. Further the age limit is chosen also due to the effect on enzalutamide on hormonal effects including unknow risk in fertility and teratogenicity.

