**Virus load assessment:**

PCR based SARS-CoV-2 measurement from upper respiratory tract.

The tests will be handled in the clinic where the patients is admitted at day 0, 2, 4 and 6. If the patient is discharged before day 6, the last test will be taken at the day of discharge.

Only the relative change of the PCR will compared for the patient and therefore the PCR will be performed at the same day after all sample have been collected at the labs used by the local clinic where the samples has been taken, or transferred to a central study laboratory

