### Primary objective

Time to discharge will be compared using the ordinal scale, between study arms using Cox regression adjusting for site, age and gender.

Time to need of mechanical ventilation or death will be compared using the ordinal scale, between study arms using Cox regression adjusting for site and gender.

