### Secondary objectives

Frequencies of Adverse events will be compared between the two arms using Fisher’s exact test.

Duration of supplemental oxygen (days) will compared between study arms using linear regression adjusted for gender and site.

Time to need of mechanical ventilation will be compared using the ordinal scale, between study arms using Cox regression. And the frequency of need of mechanical ventilation in the two arms will be tested using Fisher’s exact test.

Laboratory assessments at each time of measurement will be compared to baseline and extreme value and differences between study arms evaluated using linear or generalized linear regression adjusting for site, age and gender.

The change in viral load on day 2, 4 and 6 as compared to baseline will be compared between study arms. Also, the maximum decrease in viral load will be calculated, as the difference between observed value and maximal observed value, and compared between study arms. The analyses will be performed using linear regression adjusting for site and gender.

Total hospital stay (days) evaluated at 30 days and 6 months will be compared between groups using linear regression adjusting for site, age and gender.

Frequency of re-admission to hospital due to rebound COVID-19 will be compared between study arms using Fisher’s exact test.

Time to death will be compared between study arms using Cox regression adjusting for site and gender.

Hormonal status at 6 months will be compared to normal reference values and compared between study arms.

Frequency of serological immunity for Covid-19 will be compared between the study arms using Fisher’s exact test.

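### Covariates recorded at day 0 are left out of the models without a reason (age from ventilation-or-death, oxygen status from both primaries, the day-0 value from viral-load and laboratory models), and the maximum viral decrease is loosely defined

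*Protocol*

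**What the plan says.** Section 10.2.1, Primary objective, gives each primary endpoint its own covariate list. For discharge: "Time to discharge will be compared using the ordinal scale, between study arms using Cox regression adjusting for site, age and gender". For the other primary endpoint the protocol reads: "Time to need of mechanical ventilation or death will be compared using the ordinal scale, between study arms using Cox regression adjusting for site", with gender as the only other covariate. The difference is not explained. The section on the rationale for the patient cohort states: "Risk of having worsening symptoms has been shown to be in association with higher age and/or other risk factors".

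Section 10.2.1, Secondary objectives, sets the laboratory analysis: "Laboratory assessments at each time of measurement will be compared to baseline and extreme value and differences between study arms" are evaluated by regression on site, age and gender. Viral load is taken as change from baseline on days 2, 4 and 6. A maximum decrease is added, defined "as the difference between observed value and maximal observed value". For both viral-load measures: "The analyses will be performed using linear regression adjusting for site and gender".

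The virus load assessment paragraph in section 8.1.2 sets the swab days (0, 2, 4, 6) and adds: "If the patient is discharged before day 6, the last test will be taken at the day of discharge".

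The Randomization section stratifies by centre and gender only.

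**The concern.** Patients may enter anywhere from no oxygen need to help with respiration, and both primary endpoints are steps on a scale of oxygen and ventilation need. The starting step should therefore predict both outcomes. Age is linked to worsening by the protocol itself, yet it is left out of the endpoint that measures worsening. Neither factor is balanced by stratification.

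Leaving out strong predictors from a Cox model lowers power and moves the estimated hazard ratio towards 1 relative to the ratio among patients alike in those predictors. The two primary hazard ratios would also rest on different adjustment sets. For viral load and laboratory values, a change score without the baseline covariate is noisier than it needs to be.

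The maximum decrease is a separate matter. A quantity built on an extreme over the available samples depends on how many samples there are, and here that number depends on length of stay.

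**Working it through.** **1. Covariate lists side by side** (section 10.2.1)

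| Analysis | Covariates listed | Recorded at day 0, not a covariate |
|---|---|---|
| Time to discharge (primary) | site, age, gender | oxygen status |
| Ventilation or death (primary) | site, gender | age, oxygen status |
| Time to death | site, gender | age, oxygen status |
| Laboratory values | site, age, gender | day-0 laboratory value |
| Viral load | site, gender | day-0 viral load, age |

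Age is on the day-0 form (evaluation of other risk factors). Oxygen supply is noted at the day-0 clinical evaluation (section 8.2). Blood and swab samples are taken at day 0 (biological sampling procedures). Nothing new has to be collected.

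**2. Power of the ventilation-or-death model.** The protocol states no power, event rate or effect size, so there is no figure to reproduce and every input here is assumed: 600 patients (the Synopsis ceiling), 2:1 allocation, exponential times to day 30, and two-sided 0.025 (Bonferroni over two endpoints from an assumed overall 0.05). The models compared are gender alone against gender, age and a three-level oxygen category. Site was left out of the simulated models.

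| HR per decade / per oxygen category | Control events | True HR | Power without → with | Mean HR without → with |
|---|---|---|---|---|
| 1.3 / 1.5 | 15% | 0.55 | 57% → 59% | 0.55 → 0.54 |
| 1.3 / 1.5 | 25% | 0.55 | 80% → 82% | 0.54 → 0.54 |
| 1.5 / 2.0 | 20% | 0.60 | 53% → 55% | not tabulated |
| 1.5 / 2.5 | 15% | 0.55 | 55% → 58% | 0.56 → 0.55 |
| 1.5 / 2.5 | 25% | 0.55 | 70% → 77% | 0.57 → 0.55 |
| 1.8 / 3.0 | 20% | 0.60 | 46% → 56% | not tabulated |
| 1.8 / 3.0 | 30% | 0.60 | 65% → 75% | not tabulated |
| 2.0 / 4.0 | 15% | 0.55 | 46% → 58% | 0.59 → 0.55 |
| 2.0 / 4.0 | 25% | 0.55 | 65% → 81% | 0.60 → 0.54 |

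Rows with HR 0.55 use 300 to 400 simulated trials and rows with HR 0.60 use 800, so each single power carries a Monte Carlo error of 2 to 3 points. Both models were fitted to the same simulated data. Where age alone was added (the HR 0.55 rows), the gain was about 1 to 5 points. Most of the gain comes from oxygen status.

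**3. Type I error.** With a true HR of 1, predictors of 1.8 and 3.0 and 20% events, the model without age and oxygen rejected in 1.7% of trials at 600 patients and 1.2% at 100, against a nominal 2.5%. There is no inflation.

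**4. Baseline as a covariate.** Let the day-0 and later values have equal variance (set to 1) and correlation r.

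- Variance of the change score: 2(1−r).
- Residual variance with the day-0 value as covariate: 1−r².
- Ratio: (1−r²)/[2(1−r)] = (1+r)/2.

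This is 0.60 at r = 0.2, 0.65 at 0.3, 0.75 at 0.5 and 0.85 at 0.7. The change score therefore needs 1/0.65 = 1.54, 1/0.75 = 1.33 or 1/0.85 = 1.18 times the patients at r = 0.3, 0.5 or 0.7. At 100 patients, 2:1, a 0.5 SD effect and two-sided 0.05, power is 51% → 70%, 65% → 78% and 86% → 91% respectively.

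**5. Maximum decrease and swab count.** By the sampling rule, discharge by day 2 leaves at most two swabs. Discharge on day 3 gives days 0, 2, 3 and on day 4 gives days 0, 2, 4: three swabs. Discharge on day 5 gives days 0, 2, 4, 5, and day 6 or later also gives four. Suppose viral load is flat with independent normal noise of SD 1:

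| Swabs | Maximum minus minimum | Maximum minus last value (half of it) |
|---|---|---|
| 2 | 1.13 | 0.56 |
| 3 | 1.69 | 0.85 |
| 4 | 2.06 | 1.03 |

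Under either reading, a patient with no viral change scores a decrease, and the score grows with the number of swabs.

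**The case against.** Site and gender are exactly the randomisation strata, and adjusting for those alone is a standard, valid choice. Further covariates are a matter of efficiency. That stands, and it sets the limit of this point. A reader might infer that a chance imbalance in oxygen need would be taken for a drug effect. Such imbalances can be large in the early phases: if 20% enter on the highest support (assumed), the 95% range of the difference between arms is 1.96 × √[0.2 × 0.8 × (1/30 + 1/15)] = ±25 percentage points at 45 patients. But the test already allows for them, as the null simulations show.

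The power loss depends on assumed prognostic strength, and with weak predictors it is about 2 points. The full-trial size is to be set from prolongation data by simulation with Cox regression, so lost precision could be bought back with patients. That is true up to the ceiling of 600, but patients cost more than a covariate already on file.

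A reader might also take the viral-load and laboratory analyses to ignore baseline. They do not: it is the reference for change and is missing only as a covariate.

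It is tempting to say that the maximum decrease can have the wrong sign, since a steady rise from day 0 to day 6 could count as a fall. That needs the maximum-minus-minimum reading. If the observed value is the last one, a steady rise gives zero. The text settles neither reading. Two swabs against four is also the extreme contrast, and the arms differ through swab count only if length of stay differs. Time to discharge is, however, a primary endpoint on which a difference is hoped for.

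Few events in the early phases could justify a small model. The protocol does not say so, and site terms in a multicentre trial can use more parameters than age and one oxygen term. The 7-point scale is not expressly scheduled for day 0, but its form is completed in hospital and oxygen supply is noted that day. A separate analysis plan, not available here, could add covariates, but the protocol itself fixes these lists.

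**Conclusion.** The point holds as one of precision and consistency. The unexplained absence of age from one of two primary models is plain on the text. The absence of day-0 oxygen status from both matters more for power. At 600 patients the loss is about 2 points with weak predictors and 10 to 16 with strong ones, and the estimated hazard ratio moves from 0.55 to as much as 0.60. All of this rests on assumed event rates, effects and prognostic strengths. Baseline adjustment would leave 60% to 85% of the change-score variance for r between 0.2 and 0.7, assuming equal variances. The documents do not support calling the primary test biased or its type I error inflated.

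The maximum decrease is insufficiently defined: neither the observed value nor the order of the two values is fixed. Under both readings it depends on swab count, and so on length of stay.

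**What to change.** - **Primary endpoints.** Use one pre-specified set in both Cox models: site, gender, age (continuous) and day-0 oxygen or ordinal category. State that the 7-point category, or the oxygen status that defines it, is recorded at day 0. Use the same model in the simulations that size the full trial.
- **Viral load and laboratory values.** Add the day-0 value as a covariate at each day.
- **Maximum decrease.** Preferably drop it, since the day 2, 4 and 6 comparisons are already planned. If it is kept, define it as the day-0 value minus the lowest later value. This fixes the direction but not the dependence on swab count: with flat load and noise SD 1 it averages 0 with one later swab, 1.13/2 = 0.56 with two and 1.69/2 = 0.85 with three.
- **Fisher's exact tests.** Leave them as they are. Nothing here supports replacing them with stratified tests.

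The cost is wording and one to three extra parameters per primary model. That matters only where events are few: at 100 patients, event rates of 15% to 25% (assumed) would give 15 to 25 events.

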### Secondary objectives

Frequencies of Adverse events will be compared between the two arms using Fisher’s exact test.

Duration of supplemental oxygen (days) will compared between study arms using linear regression adjusted for gender and site.

Time to need of mechanical ventilation will be compared using the ordinal scale, between study arms using Cox regression. And the frequency of need of mechanical ventilation in the two arms will be tested using Fisher’s exact test.

Laboratory assessments at each time of measurement will be compared to baseline and extreme value and differences between study arms evaluated using linear or generalized linear regression adjusting for site, age and gender.

The change in viral load on day 2, 4 and 6 as compared to baseline will be compared between study arms. Also, the maximum decrease in viral load will be calculated, as the difference between observed value and maximal observed value, and compared between study arms. The analyses will be performed using linear regression adjusting for site and gender.

Total hospital stay (days) evaluated at 30 days and 6 months will be compared between groups using linear regression adjusting for site, age and gender.

Frequency of re-admission to hospital due to rebound COVID-19 will be compared between study arms using Fisher’s exact test.

Time to death will be compared between study arms using Cox regression adjusting for site and gender.

Hormonal status at 6 months will be compared to normal reference values and compared between study arms.

Frequency of serological immunity for Covid-19 will be compared between the study arms using Fisher’s exact test.

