## Procedures and flow chart

## Biological sampling procedures

### Handling, storage, and destruction of biological samples

Blood samples with a total volume of 10 ml to analyze Hb, LPK, Differential leukocyte count, Creatinine, CRP, ASAT, ALAT, ALP, D-dimer, IL-6 will be collected at days 0, 2, 4 and 6. Blood samples to analyze testosterone and estradiol levels will be collected at day 0 and at 6 months. Samples will be analyzed by the accredited central hospital laboratory at each site and will be destroyed immediately after analysis.
In addition, blood samples with a total volume of 15 ml for biobanking will be collected at day 0, day 6 and at 6 months. If discharged before day 6, biobanking will be performed at the day of discharge.
Five ml blood samples for analysis of Covid-19 serological immunity will be collected at 6 months and analyzed by the clinical microbiology laboratory in Umeå University Hospital, Karolinska Institute or Sahlgrenska University Hospital.

Upper respiratory swab will be collected for PCR based SARS-CoV-2 measurement at days 0, 2, 4 and 6. PCR analysis will be performed by the accredited laboratory at each site or at a central study laboratory. Residual material will be biobanked.

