# Methods for measurement of endpoints for clinical efficacy and safety

## Methods for measurement of endpoints for clinical efficacy

### Primary endpoint (variable)

The ordinal scale used to evaluate the primary end-point is used in other trials for COVID-19. It is based on the level of oxygen need if hospitalized and if not hospitalized if the patient has any symptoms or are without symptoms. (See below)

If the patient is at the hospital the 7-point ordinal scale form will be filled. If not hospitalized the follow up will be by phone and registered directly in the eCRF by study personal.

Clinical status as assessed by the 7-point ordinal scale up to 30 days after inclusion:

1) Not hospitalized, no limitations on activities. D

2) Not hospitalized, limitation on activities;

3) Hospitalized, not requiring supplemental oxygen;

4) Hospitalized, requiring supplemental oxygen;

5) Hospitalized, on non-invasive ventilation or high flow oxygen devices;

6) Hospitalized, on invasive mechanical ventilation or extracorporeal membrane oxygenation (ECMO);

7) Death;

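### Viral-load change is compared on fixed days 2, 4 and 6, but swabbing stops at discharge, a primary outcome, so the day-4 and day-6 arm differences can be distorted

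*Protocol*

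**What the plan says.** Protocol section 10.2.1, Secondary objectives, sets two viral-load comparisons. The first is tied to days: "The change in viral load on day 2, 4 and 6 as compared to baseline will be compared between study arms". The second is not: "Also, the maximum decrease in viral load will be calculated, as the difference between observed value and maximal observed value, and compared between study arms". Both share one method: "The analyses will be performed using linear regression adjusting for site and gender".

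Section 8.1.2, Virus load assessment, fixes the sampling: "The tests will be handled in the clinic where the patients is admitted at day 0, 2, 4 and 6", and then "If the patient is discharged before day 6, the last test will be taken at the day of discharge". Nothing schedules a swab between discharge and day 6. Section 8.1.1 puts outcome follow-up after discharge on the telephone: "If not hospitalized the follow up will be by phone and registered directly in the eCRF by study personal".

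Discharge is itself under test. Section 10.2.1, Primary objective, says: "Time to discharge will be compared using the ordinal scale, between study arms".

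For blood, the section on handling, storage and destruction of biological samples schedules the clinical chemistry on days 0, 2, 4 and 6. Its discharge rule covers biobanking only: "If discharged before day 6, biobanking will be performed at the day of discharge".

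**The concern.** Whether a patient has a day-4 or day-6 swab depends on whether that patient is still in hospital, which is decided after randomization and is an outcome the drug is meant to improve. A patient discharged on day 3 has swabs on days 0, 2 and 3, and the protocol does not say whether the day-3 swab enters the day-4 comparison, the day-6 comparison or neither.

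If patients who clear virus quickly also go home early, and one arm goes home earlier, that arm loses more of its fast clearers from the later comparisons. A real antiviral effect would then be understated, and a drug that shortens stay without touching the virus could seem to slow clearance. The trial is non-blinded, so discharge timing could differ by arm without any viral effect.

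Viral load is a secondary endpoint, but the Explorative phase section makes finding arm differences in it a stated purpose of the first 45 patients.

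**Working it through.** **No figure to reproduce.** The protocol gives no variance, effect size, power or discharge rate for viral load. The check is therefore a comparison of the two rules, followed by an illustration with assumed inputs.

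**The rules side by side**
- Days analysed for change from baseline: 2, 4 and 6 (section 10.2.1).
- Days sampled: 0, 2, 4 and 6 while admitted, otherwise the discharge day as the last swab (section 8.1.2).
- Reading A: the discharge swab is not used in the fixed-day comparison, so day 4 and day 6 cover inpatients only.
- Reading B: the discharge swab stands in for the missed day, so one comparison mixes swabs taken at different times.

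**Assumed inputs, none from the protocol except 2:1 allocation**
- 400,000 patients per scenario.
- Change in log10 load at day d = slope × d + noise, noise SD 0.7.
- Slope = -(0.35 + 0.15u) per day, with u standard normal. Where a viral effect is assumed, enzalutamide adds -0.05 per day, so the true day-6 difference is -0.05 × 6 = -0.30.
- Discharge hazard = (ln 2 / median stay) × exp(0.7u) × HR. HR applies to the enzalutamide arm. Control median stay is 5, 7 or 10 days from randomization.

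**Share still admitted.** For a control patient with u = 0 and median stay 5 days, 2^(-6/5) = 0.44 remain at day 6; the simulation over all patients gives 0.43. Across median stays of 5 to 10 days, 55% to 73% of controls remain at day 4 and 43% to 63% at day 6. At HR 1.5 the enzalutamide arm has 31% to 52% at day 6.

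**Day-6 arm difference (enzalutamide minus control, log10; negative means faster clearance on enzalutamide; median stay 5 / 7 / 10 days)**

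| Discharge HR | True difference | Reading A, inpatients | Reading B, discharge swab stands in |
|---|---|---|---|
| 1 | 0 | -0.002 / -0.001 / -0.011 | +0.002 / +0.004 / -0.009 |
| 1.5 | 0 | +0.140 / +0.121 / +0.102 | +0.195 / +0.178 / +0.160 |
| 2 | 0 | +0.264 / +0.212 / +0.193 | +0.339 / +0.312 / +0.292 |
| 1 | -0.30 | -0.297 / -0.297 / -0.299 | -0.213 / -0.232 / -0.250 |
| 1.5 | -0.30 | -0.169 / -0.181 / -0.198 | +0.005 / -0.025 / -0.065 |

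At day 4 with HR 1.5 and no viral effect, reading A gives +0.05 to +0.08 and reading B +0.08 to +0.10. Simulation error is about 0.01.

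With HR 1.5 and a real effect, reading A loses about a third to nearly half of it: using the simulated all-patient values, (0.299 - 0.198)/0.299 = 34% and (0.308 - 0.169)/0.308 = 45%. Reading B loses most of it. Reading B understates a real effect even at HR 1, because earlier swabs allow less time for the arms to separate.

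**Does modelling all swabs help?** A second illustration assumed baseline 6 log10, slope -0.30 per day (SD 0.20), noise SD 0.7, median stay about 6.5 days and a true effect of -0.15 × 6 = -0.90 at day 6. Inpatients gave -0.75 to -0.62. A mixed model on actual sampling day, discharge swab included, gave -0.88 to -0.78. With no viral effect and about 22% shorter stay, the values were +0.16 to +0.17 and +0.08 to +0.13. The mixed-model runs used 5,000 patients, with standard error 0.05.

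A third illustration, with median stay 5 days, agreed in direction. For a true -0.90, reading A gave -0.76 to -0.59, reading B -0.47 to -0.30 and the mixed model -0.91 to -0.73. With no viral effect and HR 1.5 they gave +0.16 to +0.19, +0.16, and +0.07 to +0.14.

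Some bias remains because discharge in these scenarios follows the patient's underlying clearance, which the observed swabs only partly reveal.

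**The case against.** The strongest reply has five parts.

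1. **The plan is not limited to days 2, 4 and 6.** This is correct. The maximum decrease is tied to no day and can use the discharge swab. It does not escape the problem, because earlier discharge gives fewer and earlier swabs in which to see a decrease.

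2. **A reader might infer that the later comparisons certainly cover inpatients only.** The protocol does not say so. The discharge swab is called the last test, and the biobanking rule replaces day 6 with the discharge day, so reading B is open. Assigning off-schedule samples to visits is often left to the SAP, which is not shown. That stands, but reading B is also distorted, and no SAP can supply swabs that were never scheduled. Nor does the drop-out rule in section 10.2 settle it, since it does not mention discharged patients.

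3. **A reader might infer that the results are biased.** The documents support only that they can be. Discharge must be related to clearance and differ by arm, or treatment must change that relation. At HR 1 reading A shows essentially no bias.

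4. **The gain from the mixed model is modest.** Also correct. With no viral effect it left roughly half to four fifths of the false difference, and the gain of 0.03 to 0.09 is only 0.6 to 1.8 of the stated standard error. The simulated declines were linear, which favours the model. The third illustration points the same way, so the improvement is credible but partial.

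5. **A reader might infer that viral load drives the decisions to expand the trial.** It is a stated purpose up to 45 patients, but nothing makes it a criterion for going beyond 100. Section 10.5 names the primary outcomes for evaluation after the prolongation phase.

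**Conclusion.** The point holds as a mismatch between the sampling rule and the fixed-day comparisons. Values on days 4 and 6 depend on discharge, a primary outcome; the role of the discharge swab is undefined; and both readings can distort the arm difference.

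The size cannot be computed from the protocol. Under the first set of assumptions, at discharge HR 1.5, the false day-6 difference with no viral effect is +0.10 to +0.14 log10 among inpatients and +0.16 to +0.20 with the discharge swab standing in. A real -0.30 shrinks to between -0.17 and -0.20, or to nearly nothing, respectively. These figures rest on an assumed link between clearance and discharge and an assumed arm difference in discharge.

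The laboratory comparisons share the sampling gap on days 4 and 6. A reader might infer that they need the same model, but nothing shows that blood counts, CRP, IL-6, liver enzymes, creatinine or D-dimer follow a linear decline, so that step is not supported.

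This concerns a secondary endpoint and is worth correcting as a cheap improvement. Confidence is high in the sampling gap and low in any particular size.

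**What to change.** In section 10.2.1, Secondary objectives:

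- Make the main viral-load analysis one linear mixed model of log10 viral load (or the relative PCR measure) on actual sampling day, with arm, time, arm-by-time, site and gender. Use every swab, including the discharge-day swab, and report the arm difference in slope.
- Name the random effects in advance (intercept and slope), with a random-intercept fallback. At 2:1, 45 patients give 30 and 15 per arm, with at most four scheduled swabs each.
- Label the single-day viral-load comparisons on days 4 and 6 and the maximum decrease as descriptive, and state how a discharge-day swab is assigned in them.
- For laboratory values, only label the day-4 and day-6 comparisons as descriptive in patients still admitted.

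The cost is analysis wording; the discharge swab is already collected. The model assumes a roughly linear log decline, and it reduces the bias without removing it, so a sensitivity analysis for informative discharge is a sensible addition. Swabbing on days 4 and 6 regardless of discharge recovered the true difference in the first simulation, but it needs sampling contact after discharge, which the protocol does not plan.

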# Benefit-risk evaluation

### Potential benefits for study participants

The pre-clinical studies show that TMPRSS2 down-regulation deteriorate the possibility for the SARS-CoV-2 to infect the lung cells, due to the strong regulation of TMPRSS2 by the androgen receptor the effect of enzalutamide treatment may eradicate further replication of the virus into new lung cells with in 24 hours after enzalutamide treatment. The benefit for the patients receiving enzalutamide may lead to both shorter time at hospital with less morbidity, lower risk of transfer to ICU and lower risk of death due to COVID-19. The strong overweight for men at the ICU may be due to the higher levels of testosterone, and if the risk of ICU care would diminished to the same levels as for women this will be of great benefit for the patients and the health care system. In women this mechanism may be as important and the benefit of decreasing the number of women to have increased morbidity and/or admission to ICU would be of great benefit for the patients and the health care system.

Further if enzalutamide is beneficial for the course of the disease, this may minimize the time at hospital and risk of sequelae for the individual patient due to no need for invasive mechanical ventilation.

Further this may be beneficial for other patient in need of the space limited ICU clinics and the stress on the health care system during the pandemic COVID-19 outbreak. The costs and stress for the COVID-19 pandemic is huge and any lessening of the burden can be of pivotal importance.

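### The maximum decrease in viral load is measured from a reference that treatment can lower, so preventing a peak after day 0 shrinks or reverses the apparent benefit

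*Protocol*

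**What the plan says.** Section 10.2.1 plans two viral-load comparisons under Secondary objectives. The first is anchored at baseline: "The change in viral load on day 2, 4 and 6 as compared to baseline will be compared between study arms". The second is an additional summary: "the maximum decrease in viral load will be calculated, as the difference between observed value and maximal observed value". For both, "The analyses will be performed using linear regression adjusting for site and gender"; day-0 load is not listed as a covariate.

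The sampling section states: "Upper respiratory swab will be collected for PCR based SARS-CoV-2 measurement at days 0, 2, 4 and 6". Section 8.1.2 (Virus load assessment) adds: "If the patient is discharged before day 6, the last test will be taken at the day of discharge". Under Treatment duration, enzalutamide starts at randomization, so three of the four scheduled swabs fall after treatment has begun.

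The benefit-risk section gives the hypothesis: "the effect of enzalutamide treatment may eradicate further replication of the virus into new lung cells with in 24 hours after enzalutamide treatment". The rationale for the patient cohort says that the time of highest replication in the lung is not fully known. Under Explorative phase, differences in virus load between the arms are a stated interest of the first 45 patients.

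**The concern.** A measure of decline needs a starting point that treatment cannot move. Here the starting point is the patient's own highest value, which may come from day 2, 4 or 6. If enzalutamide works by stopping further replication, one way this could show is a lower peak or none. A lower peak lowers the reference, and a lower reference lowers the score. The arm that benefits can then appear to clear less virus.

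At stake is how one secondary, mechanistic summary is read. With 45 patients at 2:1 there are about 15 controls (45/3) in the explorative phase, so a few control peaks could drive the comparison. The two viral-load summaries could then point in opposite directions.

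**Working it through.** **Inputs from the protocol:** the formula, the swab days, the start of treatment and the baseline-anchored companion analysis. The protocol states no viral-load mean, SD, trajectory or power, so there is no figure of its own to reproduce.

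**Assumed inputs:** log10 load, day-0 mean 6, between-patient SD 1, within-patient noise SD 0.01, 0.5 or 1.0, and 200,000 simulated patients per arm.

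**Readings of the formula.** The text does not say which observed value is subtracted. Three readings were tried:
- (a) maximum minus minimum, ignoring time order;
- (b) maximum minus last value;
- (c) largest fall after the running maximum.

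**What the formula adds.** Under reading (b):

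maximum - last = (day 0 - last) + (maximum - day 0)

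The score is the fall from day 0 plus any rise above day 0. The arm difference is therefore distorted by exactly the between-arm difference in that rise.

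**Without noise.** Treated 6, 5.5, 5, 4 scores 6 - 4 = 2.0, and its fall from day 0 is also 2.0. In these profiles the lowest value is the last one and follows the peak, so all three readings agree.

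| Control (days 0, 2, 4, 6) | Control score | Treated minus control, score | Control fall from day 0 | Treated minus control, fall from day 0 |
|---|---|---|---|---|
| 6, 7, 6, 4 | 7 - 4 = 3.0 | -1.0 | 2.0 | 0.0 |
| 6, 7, 6, 4.5 | 7 - 4.5 = 2.5 | -0.5 | 1.5 | +0.5 |
| 6, 7, 6, 5 | 7 - 5 = 2.0 | 0.0 | 1.0 | +1.0 |

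**With noise.** Treated minus control on the score, range over the three readings:

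| Control | SD 0.5 | SD 1.0 | Difference in day-0 to day-6 fall |
|---|---|---|---|
| 6, 7, 6, 4 | -0.93 to -0.91 | -0.87 to -0.68 | 0.0 |
| 6, 7, 6, 4.5 | -0.43 to -0.41 | -0.37 to -0.25 | +0.5 |
| 6, 7, 6, 5 | +0.05 to +0.07 | +0.05 to +0.15 | +1.0 |

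**If only some controls peak.** Suppose 30% of controls follow 6, 7, 6, 4.5 and the rest follow the treated profile. Without noise, the true difference is 0.3 × 0.5 = +0.15 and the score gives 0.3 × (-0.5) = -0.15. The size scales with the share of patients who peak; the reversal does not depend on it.

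**If load only rises in some controls.** Assume 30% of controls rise at 0.3 log10/day, treatment flattens those patients, and all others fall at 0.3 log10/day (slope SD 0.1, noise SD 0.5). The fall from day 0 to day 6 is 0.7 × 1.8 - 0.3 × 1.8 = 0.72 for control and 0.7 × 1.8 = 1.26 for treated, a benefit of 0.54. The simulated scores are:

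| Reading | Control | Treated | Difference |
|---|---|---|---|
| (a) maximum minus minimum | 2.00 | 1.75 | -0.25 |
| (b) maximum minus last | 1.36 | 1.50 | +0.14 |
| (c) fall after running maximum | 1.47 | 1.64 | +0.17 |

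Only reading (a) reverses the sign; (b) and (c) shrink the benefit.

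**If neither arm rises.** Treated 6, 5, 4, 3 against control 6, 5.5, 5, 4.5 at SD 0.5 gives +1.3 to +1.4, against +1.5 from day 0. The distortion is small.

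**The case against.** **No evidence of a rise.** The strongest objection is that nothing in the documents shows the measured load rising after day 0. The hypothesis concerns lung cells and the unknown timing concerns the lower tract. The swab is from the upper tract, in symptomatic patients already in hospital. This stands as a limit on size: the documents cannot say how often the problem occurs. It does not make the formula sound, because a post-baseline peak is not excluded and the reference is fixed in the protocol text.

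**A sound analysis is already planned.** This also stands. For treated 6, 5.5, 5, 4 against control 6, 7, 6, 4.5, the change from baseline favours treatment by 1.5, 1.0 and 0.5 on days 2, 4 and 6. A real effect would not be hidden; one supplementary summary could contradict it.

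**A statistical analysis plan may define the observed value.** It may, and that would settle the choice among the three readings. For a load that peaks and then falls, all three share the fault.

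Three stronger readings are tempting but not supported:
- A reader might infer that any rising load scores as a larger decrease. That requires maximum minus minimum with time order ignored. Under the other two readings a pure rise scores 0 without noise, and the arm comparison keeps its sign.
- A reader might see a contradiction with "Only the relative change of the PCR will compared for the patient". A within-patient difference on a log or Ct scale is a relative change, and section 10.2.1 states no scale, so no contradiction is shown.
- A reader might extend the point to "Laboratory assessments at each time of measurement will be compared to baseline and extreme value". That sentence also names baseline, leaves the extreme undefined, and a worst value can be a legitimate laboratory summary. The same fault is not shown there.

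**Conclusion.** The point holds in a limited form. The stated reference can be a post-treatment value. If load peaks after day 0 in some patients and enzalutamide prevents this, the summary is biased against treatment under every reading tried. In the assumed examples at SD 0.5, a benefit of 0.5 log10 appears as about -0.4, and a benefit of 1.0 as about +0.05. These sizes rest entirely on assumed trajectories and on the value being a log10 load. Where day 0 is nearly always the maximum, little changes. The fault is confined to one supplementary summary of a secondary endpoint; the change-from-baseline analysis and both primary endpoints are untouched. It is worth correcting because it is a stated rule that can mislead and is easy to repair.

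**What to change.** In section 10.2.1, replace the maximal observed value with the pre-treatment day-0 value as the reference. For example, define the decrease as day-0 minus last available value on the log10 scale (sign reversed if Ct values are used), and add day-0 load as a covariate beside site and gender. If peak load is of interest, report it as a separate descriptive summary.

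Because the last swab moves to the day of discharge when that is before day 6, add a sensitivity analysis that uses all swabs at their actual days, such as a mixed model of change from day 0. No single summary avoids early discharge. With a steady fall of 0.3 log10/day, the fall to the last swab is 0.3 × 6 = 1.8 at day 6 but 0.3 × 2 = 0.6 at day 2. The time-averaged change is half of that in each case, -0.9 and -0.3.

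The cost is a short change of wording. One secondary summary is exchanged for another, with no new samples or visits.
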